## DATA ANALYSIS AND DATA INTEGRATION

The analytical objectives of MOMI are to determine the omics signatures of each week of advancing GA (*i.e.* temporal pregnancy progression), the strength of association of each omics or other analytical platform with each APO through machine learning modelling (thereby identifying unique features of each APO phenotype), and how site-specific effects can be used to inform model generalisation. Analysis will proceed systematically from using risk signatures derived from a single platform to signatures identified through integration of multiple omics risk signatures, and from individual cohorts to cross-cohort integration. The integration of phenotypic metadata, including sociodemographics and clinical variables, will further enhance the understanding of biological mechanisms underlying APOs and improve prediction of APOs.

The structural heterogeneity across global cohorts presents a central analytical challenge that will be addressed by explicit methodological safeguards against batch effects, missingness, site heterogeneity, and overfitting. The MOMI analytical framework is built on a mature and extensively validated computational pipeline developed and applied across multiple large, multi-site pregnancy cohorts, including prior MOMI studies [17,19] and in subsequent multi-omic integration and machine-learning frameworks [15,18,20,21]. In these works, we have implemented harmonised preprocessing and quality control, explicit modelling of batch and site effects, and integration strategies that preserve biological signal while mitigating technical variation (*e.g.* empirical Bayes and factor-based normalisation, network-based integration, and multi-view latent variable models). Missing data are handled through a combination of modality-aware imputation and model architectures that accommodate partially observed samples, enabling inclusion of participants with incomplete data without introducing bias.

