For non-machine learning association analyses, we will use a prespecified covariate framework grounded in clinical relevance and established epidemiologic confounders, including maternal age, body mass index, parity, GA at sampling, and study site. These variables will be incorporated within mixed-effects or hierarchical regression models to appropriately account for cohort structure and site-level heterogeneity, with model specifications defined *a prior* to avoid data-driven overfitting. To control for false-positive findings across the large number of molecular features tested, we will apply false discovery rate correction within each omics layer and, where appropriate, across integrated analyses.

Although statistical harmonisation approaches such as ComBat are effective at reducing batch effects, they may inadvertently remove meaningful biological or population-level differences between sites. Therefore, our primary framework prioritises external validation across sites as the most conservative test of reproducibility and transportability. Rather than relying solely on post hoc harmonisation, our primary strategy is to evaluate robustness and generalisability directly. Specifically, we will train models on subsets of study sites and validate them on held-out sites. This design allows us to assess real-world performance under true site-level variation, including differences in GA assessment, biospecimen handling, and sociodemographic context. This cross-site training and validation framework ensures that identified signatures are not artifacts of a single cohort, platform, or operational pipeline, but instead reflect patterns that are stable across diverse populations. Only models and associations that replicate across sites will be interpreted as biologically meaningful, providing a principled basis for pooled analyses. As a complementary, secondary analysis, we will apply ComBat-based correction and mixed-effects modelling to quantify and compare the impact of site-level harmonisation. This layered approach allows us to rigorously test whether pooled analyses are justified, distinguish technical from biological sources of heterogeneity, and preserve interpretability, while maintaining statistical rigor across structurally heterogeneous cohorts.

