The computational pipeline employs dimensionality reduction and unsupervised clustering for sample classification, followed by statistical modelling to identify signatures associated with adverse outcomes while accounting for confounding factors. Longitudinal analysis characterises trajectories during normal pregnancy progression, providing essential context for understanding pathological changes. In parallel to the statistical approaches, machine learning will be applied to identify signatures with predictive value to enable the development of assays with diagnostic and prognostic value for the identification of APOs. This multi-layered analytical strategy aims to distinguish universal molecular signatures from population-specific variations. Pathway enrichment analysis is an essential step for interpreting the results of predictive models in biological terms, particularly when the aim is to understand the molecular mechanisms of distinct APOs. The different omics platforms will employ distinct pathway analysis tools, such as KEGG Pathway Database, Gene Ontology, STRING, MetaboAnalyst, and others [56-58]. Pathway enrichment will be conducted separately for each site and APO to ensure that the localised biological processes are accurately captured. To predict APOs of interest, machine learning techniques, specifically models based on eXtreme Gradient Boosting [59], a powerful and efficient implementation of gradient boosted decision trees, will be used. For each outcome, a distinct model will be constructed at various pregnancy stages to capture the static risk at that time point. One hundred bootstrap iterations will be performed during which a subset of the patients equal to the size of the full data set will be selected randomly with replacement. This method involves repeated random sampling to split the data into training and validation sets, thus providing a thorough assessment of model performance across various data subsets.

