To control for site imbalance in a multi-country cohort, all resampling procedures will be performed using stratified bootstrapping that preserves the joint distribution of site and outcome status. Specifically, bootstrap samples will be drawn within strata defined by study site and outcome (and, where relevant, by case-cohort membership), ensuring that each resample reflects the original cohort’s structural heterogeneity. This approach maintains appropriate representation of under-represented sites and rare outcomes in each iteration, preventing dominance by large sites and reducing bias in variance estimation and model stability assessments. Stratified resampling will be used consistently for uncertainty estimation, feature stability analyses, and performance evaluation, providing a more rigorous assessment of robustness in the presence of site imbalance. The GARBH-INi data will be utilised to validate data generated by the MOMI cohorts and, *vice versa*, GARBH-INi findings may be validated using the MOMI cohort data. The performance of these predictive models will be evaluated using area under the receiver operating characteristic and the area under the precision-recall curve, as well as prevalence of the case. Multi-site analysis is a critical component of model building, ensuring that the predictive models are robust and applicable across different populations and conditions.

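### The site-by-outcome stratified bootstrap cannot prevent large sites from dominating, and its role in performance evaluation is not reconciled with the primary held-out-site validation

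*Protocol article*

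**What the plan says.** All statements are in the protocol article, section Data analysis and data integration.

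- **Resampling scheme.** The paragraph on site imbalance says that "all resampling procedures will be performed using stratified bootstrapping that preserves the joint distribution of site and outcome status", and specifies that "bootstrap samples will be drawn within strata defined by study site and outcome", with case-cohort membership added where relevant.
- **Property claimed.** "This approach maintains appropriate representation of under-represented sites and rare outcomes in each iteration, preventing dominance by large sites".
- **Use.** "Stratified resampling will be used consistently for uncertainty estimation, feature stability analyses, and performance evaluation". The preceding paragraph sets 100 bootstrap iterations, each the size of the full data set, for the gradient-boosting models, and adds: "This method involves repeated random sampling to split the data into training and validation sets".
- **Measures.** "area under the receiver operating characteristic and the area under the precision-recall curve, as well as prevalence of the case". The text does not say whether these are pooled over sites or computed per site, or whether they come from the bootstrap or from held-out sites.
- **Cross-site validation.** An earlier paragraph makes external validation across sites the primary framework: "we will train models on subsets of study sites and validate them on held-out sites". Only models that replicate across sites are to be given a biological interpretation. The GARBH-INi cohort is named as a further validation set.
- **Missing data.** Imputation and models that accept partly observed samples are described as "enabling inclusion of participants with incomplete data without introducing bias".

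**The concern.** Two statements about one procedure do not fit together. Drawing within site-by-outcome strata, each at its own size, reproduces every site's share of women and of cases. It cannot also reduce the weight of a large site. A reader who relies on the claim would think site imbalance has been dealt with when it has not.

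The second issue is which number becomes the reported performance. In the bootstrap, women from the same site are in both the training and the validation part. Outcome rates differ between sites: PE runs from 0.23% to 3.30%, and SGA from 9.55% to 34.80%. A model that recognises the site can then rank a woman from a high-rate site above one from a low-rate site without any information about her own pregnancy. An AUROC pooled over sites credits that ranking. It is of no use inside a single clinic, where all women share one site. Held-out-site validation guards against this, but the article assigns performance evaluation to the bootstrap without saying which of the two gives the headline figure.

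**Working it through.** **Inputs (Table 2).** Order: Zambia, GAPPS Bangladesh, AMANHI Bangladesh, Pakistan, Tanzania.

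- Women: 2576, 3644, 3000, 2500, 4501; sum 16 221, as stated.
- PE cases: 85, 35, 7, 39, 124; sum 290, as stated.
- The sums for preterm birth (1587), SGA (3527) and stillbirth (168) also reproduce.

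The article gives no AUROC to reproduce.

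**Step 1: what the stratified bootstrap does to site shares.** The shares of women are fixed at 15.9%, 22.5%, 18.5%, 15.4% and 27.7% in every resample. A simple bootstrap has the same expected shares. In 100 simulated simple resamples the means agreed, with a standard deviation of about 0.3 percentage points. Stratification removes that small random variation and re-weights nothing. For PE, Tanzania keeps 124/290 = 42.8% of cases and AMANHI Bangladesh 7/290 = 2.4%. Equal weighting would give each site 20%.

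**Step 2: AUROC of a score that knows only the site.** Give each woman her site's case rate. Then

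AUROC = Σᵢⱼ casesᵢ × non-casesⱼ × wᵢⱼ / (all cases × all non-cases),

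with wᵢⱼ = 1 if rateᵢ > rateⱼ, 0.5 if equal, 0 otherwise.

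For PE, the non-cases in site order are 2491, 3609, 2993, 2461 and 4377 (sum 15 931).

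- Pairs ranked correctly across sites: 85 × 13 440 + 124 × 9063 + 39 × 6602 + 35 × 2993 = 2 628 445.
- Half credit for pairs within a site: 0.5 × 997 728 = 498 864.
- All pairs: 290 × 15 931 = 4 619 990.
- AUROC = (2 628 445 + 498 864) / 4 619 990 = 0.677.
- Share of pairs within one site: 997 728 / 4 619 990 = 21.6%.

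The same calculation for the other outcomes, with the mean over women left out of 100 simulated stratified resamples:

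| Outcome | Site rates, % | Site-only AUROC, pooled | Left-out women, mean | Pairs within one site |
|---|---|---|---|---|
| Preterm birth | 5.38–14.88 | 0.604 | 0.603 | 19.6% |
| Very preterm birth | 0.38–1.75 | 0.644 | 0.645 | 19.4% |
| Stillbirth | 0.64–2.41 | 0.638 | 0.641 | 19.1% |
| SGA <10th percentile | 9.55–34.80 | 0.651 | 0.651 | 19.0% |
| PE | 0.23–3.30 | 0.677 | 0.679 | 21.6% |
| Early-onset PE | 0.10–1.36 | 0.717 | 0.725 | 19.9% |

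With GARBH-INi added as a sixth site the values are 0.583 (preterm birth), 0.639 (PE), 0.621 (SGA) and 0.640 (stillbirth).

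**Step 3: the same score within one site.** All women have the same value, every pair is a tie, and AUROC = 0.500 for each outcome. This holds for per-site scoring in the bootstrap and for a single held-out site.

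**Step 4: is every site in validation?** Nearly always, but not for very small case groups. AMANHI Bangladesh has 3 early-onset PE cases. The chance that all three are drawn, leaving none for validation, is 3!/3³ = 22%.

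**Step 5: late samples.** Table 1 puts the AMANHI late visit at 32–36 weeks. Births before that window number 40 + 20 + 29 = 89 of 366 + 372 + 242 = 980 AMANHI preterm births (very preterm row of Table 2), or 9.1%. These women cannot have the sample. This is a floor, since others deliver inside the window before their visit.

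**The case against.** The strongest reply is that the safeguard is already there. Held-out-site validation is the declared primary framework, replication across sites is a condition for interpretation, and GARBH-INi is a further check. A bootstrap can sit beside these as internal validation, and the article calls its approach layered. This stands. A reader might infer that the bootstrap AUROC is the planned headline and that the two schemes are incompatible; the text supports neither. What it leaves open is how they relate.

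The inflation also needs two conditions that the article does not state: one AUROC pooled over sites, and features that reveal the site. Site enters as a prespecified covariate only for the association analyses outside machine learning. The pipeline is, however, described as modelling batch and site effects, and a ComBat comparison is planned as a secondary analysis. The figures in the table are therefore ceilings.

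It is also tempting to say that large sites dominate. No site holds a majority of cases for any outcome. Tanzania, the largest, supplies 15.2% of preterm births (242/1587) and 12.2% of SGA (430/3527). Zambia, the second smallest, supplies 36.9% of stillbirths (62/168) and 46.1% of early-onset PE (35/76). The error lies in the property claimed. The wide PE contrast also leans on one site with 7 cases: against the next lowest rate (0.96%), Zambia's 3.30% is 3.4 times as high.

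On late samples, a reader might infer a definite amount of leakage. Nothing says that visits after delivery will be imputed or that missingness will serve as a predictor, and the gestational-age distribution needed to size the effect is not given.

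**Conclusion.** The point holds in a limited form. The claim that the stratified bootstrap stops large sites from dominating is wrong as written, because the scheme keeps every site's share exactly. This follows from the article's own description and needs no assumption.

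The use of the bootstrap for performance evaluation is not reconciled with held-out-site validation. If its AUROC were pooled, site alone could produce anything from 0.50 (site not recognisable) to 0.60 for preterm birth, 0.64 for very preterm birth and stillbirth, 0.65 for SGA, 0.68 for PE and 0.72 for early-onset PE. These ceilings assume the full-cohort counts of Table 2, pooling over the five sites, and features that identify site perfectly. Separately scored held-out sites are not open to this inflation; an AUROC pooled over several held-out sites could be.

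The blanket assurance that incomplete data bring no bias is a secondary matter. At the AMANHI late visit, absence of a sample depends on the outcome for at least 9.1% of preterm births. The effect on model performance is not established.

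**What to change.** 1. Delete the statement about large sites, or replace it by saying that stratification keeps each site's share fixed across resamples.
2. State that held-out-site AUROC, scored per site and then combined, is the headline performance measure.
3. Label the stratified bootstrap as internal validation, feature stability and interval estimation.
4. Compute any bootstrap AUROC within site, and show it beside a site-only benchmark.
5. Qualify the assurance about missing data, and limit each time-point model to women still pregnant and sampled at that visit.

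No new data are needed. The cost is additional analysis runs and probably lower reported AUROCs.

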### Frequencies of APOs

After applying the data harmonisation results, we found that approximately 34% of all pregnancies in the MOMI cohort were affected by adverse outcomes (**Table 2**). Pregnant women in Tanzania experienced the fewest number of APOs (18.33%), whereas pregnancies in women of the other two AMANHI sites (Bangladesh and Pakistan) resulted in the highest numbers of APOs (47.94% and 45.00%, respectively). SGA was the most common APO in the combined MOMI cohort (n = 3527, 21.74% of pregnancies), as well as at each site. PTB was observed in close to 10% of all pregnancies, ranging from 5.4% in Tanzania to 14.9% in Pakistan. PE and SB cases ranged from 0.23% to 3.30% and from 0.64% to 2.41%, respectively. The frequencies of the distinct APOs in the GARBH-INi cohort mirrored those observed in the MOMI cohort (**Table 2**).

**Table 2 T2:** Frequencies of adverse pregnancy outcomes

	GAPPS		AMANHI			Combined MOMI cohort	GARBH-INi
	**Zambia**	**Bangladesh**	**Bangladesh**	**Pakistan**	**Tanzania**		
**Number of Pregnancies**	2576	3644	3000	2500	4501	16 221	8100
**APO**	**Number of APOs (% of pregnancies)**						
**PTB**	223 (8.66)	384 (10.54)	366 (12.20)	372 (14.88)	242 (5.38)	1587 (9.78)	764 (9.43)
Very PTB (% PTB)*	45 (20.0)	14 (3.6)	40 (10.9)	20 (5.4)	29 (11.9)	148	72 (9.4)
**PE**	85 (3.30)	35 (0.96)	7 (0.23)	39 (1.56)	124^c^(2.75)	290 (1.79)	166 (2.05)
Early-onset PE (% PE)	35 (41.2)	7 (20.0)	3 (42.8)	9 (23.1)	22 (17.7)	76	13 (8.6)
Late-onset PE (% PE)	50 (58.8)	28 (80.0)	4 (57.2)	30 (76.9)	100 (80.6)	212	151 (91.0)

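### The named performance measures do not assess calibration, so held-out-site validation can show that a ranking transports but not that predicted risks do

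*Protocol article*

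**What the plan says.** All of this is in the Protocol article, mostly under Data Analysis and Data Integration.

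- **Measures.** "The performance of these predictive models will be evaluated using area under the receiver operating characteristic and the area under the precision-recall curve", and the sentence goes on: "as well as prevalence of the case". The article names no calibration measure, no comparison of predicted with observed risk and no recalibration step.
- **Validation design.** "we will train models on subsets of study sites and validate them on held-out sites". The splits are not specified.
- **What validation is said to show.** "our primary framework prioritises external validation across sites as the most conservative test of reproducibility and transportability", and "This design allows us to assess real-world performance under true site-level variation". After naming the measures, the same section says that multi-site analysis makes the models robust and applicable in different populations.
- **What the models produce.** For each outcome, "a distinct model will be constructed at various pregnancy stages to capture the static risk at that time point". The introduction also names risk assessment tools and better-informed risk prediction models among the aims.
- **Site differences.** Under Frequencies of APOs: "PE and SB cases ranged from 0.23% to 3.30% and from 0.64% to 2.41%, respectively". Table 2 gives the counts by site.

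**The concern.** AUROC depends only on the order of the predicted risks. AUPRC depends on that order and on the case fraction in the validation data. Neither changes when every prediction is shifted or rescaled in a way that keeps the order. Case prevalence describes the data, and the article does not set it against the mean predicted risk.

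A claim that risk transports needs more. At the new site, women given a predicted risk of 2% should have the outcome about 2% of the time. With base rates as different as those in Table 2, this is where a model moved between sites is most likely to fail. The stated measures would not show the failure, and a model could be called applicable across populations on evidence about ranking alone.

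**Working it through.** **Inputs (Table 2).** Pregnancies: Zambia 2576, GAPPS Bangladesh 3644, AMANHI Bangladesh 3000, Pakistan 2500, Tanzania 4501; total 16 221. PE cases in the same order: 85, 35, 7, 39, 124; total 290. SGA below the 10th percentile: 3527 in total, 430 at Tanzania.

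**Step 1: reproduce the article's figures.** PE combined: 290/16 221 = 1.79%. By site: 3.30%, 0.96%, 0.23%, 1.56%, 2.75%. SGA: 3527/16 221 = 21.74%; Tanzania 430/4501 = 9.55%. All agree with Table 2. The PE range is 3.30%/0.233%, about 14-fold.

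**Step 2: leave one site out.** Expected rate = (total cases − site cases)/(total pregnancies − site pregnancies). Expected/observed (E/O) = expected rate/site rate. This takes the mean predicted risk at the held-out site to equal the outcome rate of the four training sites.

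| Outcome, held-out site | Expected | Observed | E/O |
|---|---|---|---|
| PE, Zambia | 205/13 645 = 1.50% | 3.30% | 0.46 |
| PE, GAPPS Bangladesh | 255/12 577 = 2.03% | 0.96% | 2.11 |
| PE, AMANHI Bangladesh | 283/13 221 = 2.14% | 0.233% | 9.17 |
| PE, Pakistan | 251/13 721 = 1.83% | 1.56% | 1.17 |
| PE, Tanzania | 166/11 720 = 1.42% | 2.75% | 0.51 |
| SGA, Tanzania | 3097/11 720 = 26.4% | 9.55% | 2.77 |

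For PE the error is about two-fold or more at four of the five sites, and it goes in both directions. At Zambia, 3.30/1.50 = 2.2-fold under-prediction.

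**Step 3: precision.** At AMANHI Bangladesh, 64.2 PE cases would be predicted against 7 seen. The exact 95% interval for 7/3000 puts E/O between 4.5 and 22.8. Because the article does not fix the splits, all training subsets of the other four sites were tried; E/O at this site runs from 4.1 (trained on GAPPS Bangladesh alone) to 14.1 (Zambia alone). For SGA at Tanzania the interval is 2.5 to 3.0, so that figure does not rest on small numbers.

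**Step 4: do the named measures react?** In a simulation of 300 000 records with one normal predictor and a logistic slope of 1.2 (assumed), outcomes were drawn at a mean risk of 7/3000. They were scored once with correct risks and once with the intercept moved so that mean risk was 283/13 221. AUROC was 0.796 both times and average precision 0.0142 both times, while simulated E/O was 9.0. At the training-site base rate, average precision was 0.108. AUPRC therefore does fall at the low-frequency site, but by the same amount when the risks are correct, so the fall does not reveal the error.

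**Step 5: the slope alone is not enough.** The error in step 4 is a pure intercept shift, so the calibration slope stays at 1. Only a comparison of total expected with total observed cases detects it.

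**Step 6: GARBH-INi.** On the same assumption, a stillbirth model trained on all five MOMI sites would predict 168/16 221 = 1.04% against 168/8100 = 2.07% (E/O 0.50).

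**The case against.** The best case for the plan has four parts.

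1. **The list of measures is a summary sentence in an article.** It does not say that it is complete, and a fuller analysis plan could add calibration. This stands in part: a reader might infer that calibration has been ruled out, and nothing in the text says so. But the article does name its measures and draws conclusions about applicability from the validation, and the named measures cannot carry those conclusions.
2. **The measures are not all about ranking.** A reader who stops at the precision-recall curve might infer that they are. The sentence goes on to name case prevalence, which gives the AUPRC baseline and shows that base rates will be reported. It is not compared with predicted risk, so the gap remains.
3. **The stated pass rule concerns biology.** Models and associations that replicate across sites are to be read as biologically meaningful, and machine learning is meant to find signatures for later assay development. Discrimination suits that purpose, and this objection stands in full. The article sets no step at which a model is released as a risk calculator.
4. **Nine-fold is a selected extreme.** This stands. It is the largest of the five PE ratios, rests on 7 cases and depends on a split that the article does not fix. A reader might infer that PE risks will be nine times too high at that site. Table 2 does not show this, because molecular and clinical features may explain part of the difference between sites.

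**Conclusion.** The point holds as a mismatch between stated measures and stated claims. AUROC, AUPRC and case prevalence can support transportable ranking. They cannot support transportable risk, real-world performance of a risk model, or applicability across populations. The rule on biologically meaningful replication is not affected.

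The possible size is an over-prediction of about 2.8-fold for SGA at Tanzania, an under-prediction of about 2.2-fold for PE at Zambia and, at worst, an over-prediction of about nine-fold for PE at AMANHI Bangladesh (4.5 to 22.8). These figures assume leave-one-site-out splits, training predictions that reflect full-cohort frequencies, features that explain none of the site difference, and no recalibration. They show what could go unseen; they do not forecast what will happen. That a shift in overall risk level leaves AUROC and AUPRC unchanged needs none of these assumptions.

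**What to change.** In Data Analysis and Data Integration, after the sentence naming the performance measures, add for every held-out site and for GARBH-INi:

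- the observed/expected ratio (the inverse of the E/O above) with a confidence interval, and the calibration slope;
- both taken before any recalibration, because updating the intercept brings observed/expected to about 1 by construction and leaves the slope as it was;
- case-cohort weights wherever sub-cohort samples are used, because those samples are enriched for cases and unweighted ratios would mislead.

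Then tie the wording to the results, with acceptable limits set in advance:

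- transportable for risk only if discrimination, observed/expected ratio and slope are all acceptable;
- in need of site-specific recalibration if only the observed/expected ratio fails;
- otherwise, where discrimination holds, transportable in ranking only.

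The cost is small: the work uses predictions that will already exist and needs no new assays. Some models will be described less favourably. Estimates will be imprecise where cases are few; with 7 PE cases at AMANHI Bangladesh a slope would say very little, and the report should state this.
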